## Methods and analysis

### Study design and timeline

This is an investigator-initiated prospective, multicentre, randomised, open-label, two-arm clinical study. In total 186 patients will be randomised 1:1 to the experimental or control arm (figure 1). LT in the context of regular organ allocation can be performed in both arms according to the centre’s decision, that is, using static cold storage, hypothermic or NMP for organ preservation. Quality assessment of grafts judged clinically unacceptable by NMP is reserved for the experimental arm.

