#### Quality assessment

Declined liver grafts considered for quality assessment must not have macrovesicular steatosis >60%, fibrosis grade >F3 or cirrhosis (based on histopathologic quick section analysis, if requested by the responsible transplant surgeon after macroscopic examination) and have a graft weight between 1 and 2.5 kg. Moreover, grafts must be connectable in terms of vascular anatomy. The goal is to maintain a dropout rate of no more than 50% for grafts that either fail quality assessment via NMP or cannot be safely transplanted despite undergoing NMP quality assessment. Additionally, the organ must not yet have been treated using a dynamic preservation procedure (HOPE or NMP).

As part of the ExTra LT quality assessment, the liver is removed from the cold preservation solution in the transplant centre in an end-ischaemic ‘back-to-base’ approach, prepared, cannulated and connected to the liver perfusion machine according to the respective manufacturer’s specifications. The decision to use or reject a graft after quality assessment by NMP (ie, start of recipient hepatectomy) is made at least 4 hours after the start of perfusion by the transplant surgeon, based on:

Lactate levels <2.5 mmol/L.And two or more of the following:Evidence of bile production.Maintenance of a perfusate pH >7.30 (without correction for at least 1 hour).Glucose metabolism (falling perfusate glucose value with consistent downward trend).Maintenance of stable arterial and portal venous flows (if using OrganOx Metra: 150 and 500 mL/min, respectively).Homogeneous perfusion with soft consistency of the parenchyma.

If the liver fulfils the above criteria after 4 hours of perfusion and is assessed as safely transplantable based on the assessment of the transplant surgeon in charge, the recipient is then initiated for surgery and the liver is transplanted. The quality assessment is device-independent (currently usable: XVIVO LiverAssist, OrganOx Metra or Aferetica PerLife). Additionally, a combination of HOPE and COR prior to the 4 hours of quality assessment with NMP is possible.

If patients are not transplanted within 12 months, they continue to be regularly listed on the waiting list without the possibility for an ExTra-LT and are censored.

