#### Secondary endpoints

The secondary endpoints include, among others, competing events (death, disease progression, recovery) and are also evaluated on the intention-to-treat cohort. Again, the time from randomisation until the occurrence of the event is examined. For death (corresponds to waiting list mortality) and the composite of disease progression and recovery, cause-specific Cox proportional hazards models are calculated. The same variables as for the primary endpoint are used for adjustment (reMELD-Na score and waiting time), in addition to perfusion device used (OrganOx Metra, LiverAssist or Aferetica PerLife), study centre, age and sex. Furthermore, of particular interest are the number of patients still listed for transplantation after 12 months, the overall patient survival (from randomisation to death), the quality of life (EuroQol-5 Dimension, 5-Level questionnaire - EQ-5D-5L), the graft utilisation rate (used organs/offered organs for patients on the waiting list) as well as transplantation-associated costs.

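### The secondary Cox models for waiting-list death and for progression/recovery adjust for perfusion device, a post-randomisation variable that can bias the arm effect against the experimental arm or leave the model unfittable

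*Protocol article*

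**What the plan says.** Under Secondary endpoints, the protocol article states: "For death (corresponds to waiting list mortality) and the composite of disease progression and recovery, cause-specific Cox proportional hazards models are calculated". The competing events "are also evaluated on the intention-to-treat cohort", and "the time from randomisation until the occurrence of the event is examined". For covariates it says "The same variables as for the primary endpoint are used for adjustment (reMELD-Na score and waiting time"), and then adds "in addition to perfusion device used (OrganOx Metra, LiverAssist or Aferetica PerLife), study centre, age and sex".

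Two other sections show when a device value can arise. Under Quality assessment, the graft is taken to the transplant centre and there "prepared, cannulated and connected to the liver perfusion machine according to the respective manufacturer’s specifications". Under Study design and timeline, "Quality assessment of grafts judged clinically unacceptable by NMP is reserved for the experimental arm", while regular transplants in either arm may be done "using static cold storage, hypothermic or NMP for organ preservation".

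The article names three devices. It gives no level for patients without one, no time-dependent coding and no restriction to transplanted patients.

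**The concern.** Baseline reMELD-Na, prior waiting time, centre, age and sex can all be known at randomisation. The device cannot. It becomes known when a graft is perfused, so it depends on the arm and on having survived on the list long enough to get an organ. A patient who dies, progresses or recovers while listed will normally have no device. A patient transplanted with a perfused graft leaves the risk set for those events. Adjusting for device therefore conditions on the future, inside a comparison described as intention-to-treat.

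Waiting-list mortality is a main secondary measure of whether the ExTra option helps patients. The distortion runs against the experimental arm, because that arm has the additional transplants with perfused grafts. A neutral effect on waiting-list death could look like harm.

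**Working it through.** **Inputs.** From Sample size: monthly transplant hazard 0.057 (control) and 0.104 (experimental); competing-event hazard 0.0251 in both arms, so the true hazard ratio (HR) for waiting-list events is 1.00; 83 per group, 93 after dropout. Follow-up for these events is 12 months. Assumptions not in the document: all additional transplants (0.104 − 0.057 = 0.047 per month) use a device; a share f of regular transplants do, varied from 0 to 1; device use is unrelated to prognosis; death is half of competing events where death is modelled alone.

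**1. The plan's own figures.** With s = transplant hazard + competing hazard, and S = exp(−12s):
- Control: s = 0.0821, S = 0.373. Transplanted 0.057/0.0821 × 0.627 = 43.5%; competing event 0.0251/0.0821 × 0.627 = 19.2%; still listed 37.3%. The article gives 43.6%, 19.1% and 37.2%.
- Experimental: s = 0.1291, S = 0.212. Transplanted 0.104/0.1291 × 0.788 = 63.4% (article 63.6%); competing event 15.3%.
- Simulated Cox power at 83 per arm is 0.804, with a median of 36 control transplants and 17 additional (4 to 29), as stated. 83/0.9 = 92.2, rounded up to 93.

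The data model below is therefore the protocol's own.

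**2. What the device term does.** Take device as a fixed covariate with levels "used" and "none". In simulation, patients with a device had 0 waiting-list events in every scenario. The device coefficient then has no finite estimate: one fit at f = 0.25 returned a log HR of about −40 with a standard error of about 4 × 10⁷. In the limit, the fit equals one with all device recipients removed from the risk sets.

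**3. Size by hand (person-time).** Expected months at risk per patient are (1 − S)/s: 7.63 in control and 6.10 in experimental. Mean time to event, given an event by month 12, is 1/s − 12S/(1 − S): 5.03 and 4.51 months.
- f = 0: experimental device recipients are 0.047/0.1291 × 0.788 = 28.7%, control 0%. Months lost are 0.287 × 4.51 = 1.29. The experimental rate becomes 0.1531/(6.10 − 1.29) = 0.0318, against 0.0251 in control. Ratio 1.27.
- f = 1: control loses 0.435 × 5.03 = 2.19 months, giving 0.1916/(7.63 − 2.19) = 0.0352. Experimental loses 0.634 × 4.51 = 2.86, giving 0.1531/(6.10 − 2.86) = 0.0473. Ratio 1.34.

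**4. Size by Cox fit (500,000 per arm, all competing events).**

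| f | Device recipients, control / experimental | HR without device | HR with device |
|---|---|---|---|
| 0 | 0% / 29% | 1.00 | 1.27 |
| 0.25 | 11% / 37% | 1.00 | 1.28 |
| 0.5 | 22% / 46% | 1.00 | 1.29 |
| 1 | 44% / 64% | 1.00 | 1.33 |

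For death alone, at half of competing events, the HR with device is 1.26 to 1.32.

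**5. At trial size (93 per arm, 4,000 simulated trials per scenario, two-sided 5%).**
- All competing events together (about 32): rejection 4–5% without the term, about 10–13% with it.
- Death at half of competing events (about 16): 3–4% without, about 7% with it (6.4% to 8.5% over f).

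The plan models death and the composite separately. The pooled figure is therefore the limit in which nearly all competing events fall in one model.

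**6. The other simple coding.** If patients with no device are dropped as missing, the analysis keeps only device recipients. Almost no waiting-list events remain and the model cannot be fitted.

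**The case against.** The strongest reply is that the biased HR depends on a coding the article does not state, and that coding commonly belongs in the analysis plan, which is not shown. Device might be meant as a time-dependent term with follow-up ending at transplant, or as a centre-level attribute. Neither would bias the arm effect in this way. That stands, and the HR range above is conditional for this reason. It does not rescue the term. The text speaks of the device used and gives neither reading. A centre-level device would largely overlap with study centre, already in the model, and a time-dependent term ending at transplant would add next to nothing. The article states the covariate outright, so this is not a detail merely left out.

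Some stronger inferences are tempting but not supported:
- *No patient with an event can have a device value.* A graft is perfused for at least 4 hours before the decision to use it, and some will fail. An intended recipient could carry a device value and stay listed, although the article does not say this is recorded per patient. With 10% or 30% of such failures recorded (f = 0.25, half of assessed grafts accepted), the device coefficient is finite, and the arm HR is 1.32 or 1.39 against a truth of 1.00. The bias stays.
- *The model yields no result.* With a "none" level, only the device coefficient diverges. The software still prints an arm HR.
- *The trial would probably report harm.* With about 16 deaths, the standard error of the log HR is near 0.52 and the bias is log 1.27 = 0.24, under half of it. A false significant result is a minority outcome.

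**Conclusion.** The concern holds for the two secondary waiting-list models. The stated adjustment set contains a post-randomisation variable normally present only in patients who can no longer have the event. As a fixed covariate with a "none" level, it moves the arm HR from 1.00 to about 1.26–1.33 against the experimental arm, and roughly doubles false rejection for death or more than doubles it for all competing events together. With complete cases only, the model cannot be fitted. These sizes rest on the protocol's exponential hazards and on the assumed coding, device share and death share listed above. The direction was the same over the whole range of device share.

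A reader might infer that the main result is at risk too. The documents do not support that: the Secondary endpoints section lists only reMELD-Na and waiting time as the primary model's adjustment variables, and the sample size does not use device. The safety board's Kaplan-Meier review of 3-month graft and patient survival does not use this model either, and overall survival from randomisation is listed as a separate endpoint.

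**What to change.** Delete perfusion device from the adjustment set of all models for pre-transplant events (death, progression, recovery). Keep only covariates known at randomisation: reMELD-Na, prior waiting time, study centre, age and sex. Use device only in post-transplant analyses among recipients of machine-perfused grafts.

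This changes one phrase in the protocol and the matching line in the analysis plan. It needs no further data or patients, and no change to the primary analysis. It should be made before the secondary models are run.

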### Sample size

The primary statistical objective is to show that the cause-specific HR for the transplant risk between the two randomised groups is not equal to 1. The assumptions for the data-generating process are based on data from Eurotransplant in 2022: Within 12 months, 43.6% of patients with a MELD ≤25 (corresponds to reMELD-Na ≤21) who were not eligible for Standard or Non-Standard Exception were transplanted, 19.1% had a competing event (death, progression or recovery) and 37.2% remained on the waiting list and were censored in this study.

As a treatment effect, an increase in the transplantation rate of 20% to 63.6% was assumed, while the risk of the competing event remains unchanged. A 20% increase in the transplantation rate through the ExTra option is realistic, as 385 LTs were performed in Germany in 2022 in patients with MELD ≤25 without standard/non-standard exception MELD criteria, while 133 of 217 declined grafts would have been potentially acceptable after a quality assessment using NMP, representing approximately 20% additional grafts in the study population based on an estimated 50% acceptance rate following NMP.

Assuming exponential distributions for time to transplant and time to competing event, the data were simulated to fit this pattern. The parameter of the exponential distribution for time to transplant (in months) was 0.057 for the control group and 0.104 for the intervention group. The parameter for the competing risk was 0.0251 for both groups. A Cox proportional hazards model was used to estimate the transplant HR between the ExTra LT group and the control group.

Based on 1 000 000 simulations, a sample size of N=83 per group was calculated for a two-sided type I error of 0.05 and a power of 0.8. Considering a dropout rate of 10%, a total of 93 patients will be recruited per group. A median of 36 transplantations is expected in the control arm. It is expected that 4–29 additional transplantations (median: 17) will be performed in the experimental arm.

This number of cases can probably be reached with a recruitment period of 36 months. A 12-month intervention phase is planned, followed by a 12-month follow-up phase. The study will thus end when all 83 patients in each treatment group have completed the 12-month follow-up after randomisation/transplantation.

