### Study sites

In Germany, 18 of 19 LT centres have expressed their interest in participating in the study. Currently, 11 centres are actively recruiting patients.

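### Entering study centre as a fixed covariate in the two secondary competing-event Cox models leaves roughly one event or fewer per parameter and widens the arm estimate

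*Protocol article*

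**What the plan says.** The Secondary endpoints section of the protocol article specifies two cause-specific Cox models, one for death on the waiting list and one for progression and recovery combined. Both adjust for the variables of the primary analysis (reMELD-Na score and waiting time) and also for perfusion device, with three devices named, and for "study centre, age and sex". It does not say whether centre enters as indicator terms, strata or a random effect.

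The Sample size section pools the competing events: in the reference data, "19.1% had a competing event (death, progression or recovery") within 12 months. For planning, "The parameter for the competing risk was 0.0251 for both groups" (per month). No split between death and the other two types is given.

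On centre numbers, Table 1 lists 13 enrolled centres. The Study sites section says that 11 are recruiting and that "18 of 19 LT centres have expressed their interest in participating in the study". The Randomisation section stratifies by reMELD-Na and waiting time, not by centre.

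**The concern.** Two models that share about 30 events are each given a covariate with 13 to 18 levels. In a Cox model with fixed centre terms, a centre without an event has a coefficient that runs off to minus infinity. Its patients then carry no weight in the risk sets and drop out of the arm comparison. With few events this will happen in many centres, so information on the arm effect is lost and the estimate becomes unstable. The death model is the trial's stated measure of waiting-list mortality, so it should not be made less precise than the event count already makes it.

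**Working it through.** **Inputs (Sample size section).** Monthly transplant hazard "was 0.057 for the control group and 0.104 for the intervention group"; competing hazard 0.0251 in both arms; follow-up cut at 12 months; 83 per group for 80% power at a two-sided 5% level; recruitment raised to 93 per arm to allow for 10% dropout.

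**Reproducing the plan's figures.** For competing exponentials, the 12-month incidence of a cause with hazard a, where the other cause has hazard b, is a/(a+b) × (1 − exp(−12(a+b))).

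- Control transplants: 0.057/0.0821 × (1 − exp(−0.9852)) = 0.435, and 83 × 0.435 = 36.1. The article says "A median of 36 transplantations is expected in the control arm".
- Experimental transplants: 0.104/0.1291 × (1 − exp(−1.5492)) = 0.634.
- Simulated power at 83 per arm (20,000 runs): 0.802. 83/0.9 = 92.2, rounded up to 93.

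The planning model is reproduced.

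**Competing events from the same model.**

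- Control: 0.0251/0.0821 × 0.6266 = 0.192. Experimental: 0.0251/0.1291 × 0.7876 = 0.153.
- 83 per arm: 15.9 + 12.7 = 28.6 (simulated 95% range 19 to 38). 93 per arm: 17.8 + 14.2 = 32.1.
- Equal split (assumed): 14.3 to 16.0 per model. One-third/two-thirds split (assumed): 9.5 to 10.7 in one model and 19.1 to 21.4 in the other.

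**Parameters with fixed centre terms.** Arm 1 + reMELD-Na 1 + waiting time 1 + device 2 or 3 (3 if there is a level for no device) + centre 12 + age 1 + sex 1 = 19 or 20 with 13 centres. With 18 centres the centre term takes 17, giving 24 or 25.

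**Events per parameter.** Equal split: 14.3/25 = 0.57 to 16.0/19 = 0.84. Over all these splits with 13 to 18 centres: 9.5/25 = 0.38 to 21.4/19 = 1.12. With only 11 centres the maximum is 21.4/17 = 1.26.

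**Effect on the arm estimate.** Simulated trials with no arm effect on the competing event, no centre, age or sex effect, unequal centre sizes and device left out. The entries are the SD of the estimated arm log hazard ratio.

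| Centres | Events in model | Without centre | With fixed centre | Rise |
|---|---|---|---|---|
| 13 | 14 | 0.621 | 0.752 | 21% |
| 13 | 16 | 0.563 | 0.662 | 18% |
| 18 | 14 | 0.624 | 0.853 | 37% |
| 18 | 16 | 0.602 | 0.776 | 29% |

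These rows use 400 trials each, with age and sex in both models. Two further sets (500 and 600 trials per scenario, 93 per arm) compared the two randomisation factors alone with the set that adds centre, age and sex:

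- 13 centres, 16 events: 0.63 to 0.73 and 0.58 to 0.68 (16 to 17%).
- 13 centres, 10 to 11 events: 0.76 to 0.98 and 0.71 to 0.89 (25 to 29%).
- 18 centres, 16 events: 0.57 to 0.71 and 0.53 to 0.68 (25 to 28%).
- 18 centres, 10 to 11 events: 0.83 to 1.13 and 0.69 to 0.98 (36 to 42%).

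At about 21 events with 13 centres, the SD went from 0.47 to 0.56 (19%).

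Age and sex alone raised the SD by only 1 to 5%. In models with 16 events or fewer, 34 to 58% of centres had no event, depending on scenario.

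**The case against.** The strongest objection is that the article says only that centre is used for adjustment. A statistical analysis plan that is not shown could enter it as a frailty or pool small centres, and either would be compatible with the text. This stands in part: the parameter count is conditional on fixed terms. But the article does fix the covariate list, and an unqualified list for a Cox model is normally read as ordinary covariates.

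Second, the simulations contain no true centre effect, so adjustment could only cost precision. That is fair. The article expects centre differences in postoperative management, but says nothing of the kind about waiting-list outcomes.

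Third, the practical gain is limited. At an SD of 0.57 to 0.63 without centre, 80% power needs a hazard ratio of about exp(2.80 × SD) = 4.9 to 5.8, so the leaner model is imprecise too.

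A reader might infer more than the documents support:

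- **That both models could have as few as 10 events.** They share 29 to 32, so if one has 10 the other has about 19 to 21.
- **That up to half of the information is lost.** The largest losses need an assumed one-third share together with 18 centres, which is a count of expressions of interest. At about 10 events the raw SD is also driven by outlying estimates: in one check with 13 centres it was 1.22, against 0.86 from the interquartile range.
- **That age, sex and device share the blame.** Age and sex cost almost nothing, and device was counted but not simulated.
- **That the type I error is inflated.** One set of simulations gave 6 to 9% with centre, another 4 to 7%, so this is not established.

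**Conclusion.** The point holds for the two secondary models, on the condition that centre is fitted as a fixed effect. The events per parameter are then about 0.4 to 1.1 for splits between one third and two thirds and 13 to 18 centres. Over a third of centres would have no event in a model with 16 events or fewer. The SD of the arm log hazard ratio rises by roughly 15 to 25% with 13 centres (a variance 1.15² = 1.32 to 1.25² = 1.56 times as large), and by more with 18 centres or the smaller event share. Nearly all of this comes from centre.

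The size rests on the article's planning hazards, an assumed split of events, and null simulations without device. Single simulated values are rough: the SD without centre should not depend on the number of centres, yet it drifted by about 10% between runs. The direction was the same in every scenario. Because only null effects were simulated, the loss of power for a given true difference was not measured.

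The primary analysis, described as adjusting for reMELD-Na and waiting time, and the sample size are not affected.

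**What to change.** In the death model and the progression-plus-recovery model, state that study centre is not fitted as a fixed effect. Either omit it, which the randomisation scheme allows because centre is not a stratification factor, or include it as a shared frailty. Keep the randomisation factors reMELD-Na and waiting time; age and sex are optional. If a frailty was always intended, saying so settles the point.

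Under an equal split, arm plus the two randomisation factors gives 14.3/3 = 4.8 to 16.0/3 = 5.3 events per parameter. Adding age and sex gives 14.3/5 = 2.9 to 16.0/5 = 3.2. These counts also leave device out. A device is known only after randomisation and does not exist for patients who die or leave the list untransplanted, so whether it belongs in these models is a separate question.

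The cost is a change of wording while the trial is still recruiting. The downside is that centre differences are smoothed or not modelled, and at 3 to 5 events per parameter the estimates remain imprecise and should be reported as such.
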